**Absolute neutrophil count will be assessed by the physician with local analyses performed within 3 days prior to V1.**

|                                                                                   |                    |                                                                      |
|-----------------------------------------------------------------------------------|--------------------|----------------------------------------------------------------------|
| [figure not shown] | DOCUMENT    | Protocol ID : MPOH05
EudraCT N° : 2019-004253-89
Version: 10.0 |
|                                                                                   | CIMON STUDY | Date : 04 MAY 2021
Page 34 / 70                                   |

|                                                                                   |                    |                                                                      |
|-----------------------------------------------------------------------------------|--------------------|----------------------------------------------------------------------|
| [figure not shown] | DOCUMENT    | Protocol ID : MPOH05
EudraCT N° : 2019-004253-89
Version: 10.0 |
|                                                                                   | CIMON STUDY | Date : 04 MAY 2021
Page 35 / 70                                   |

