|                                                   | 
After recovering from neutropenia (neutropenia is defined as Poly-Nuclear Neutrophils count <math>\leq 0.5 \times 10^9</math> cells/L)
 
Dose regimen:
 
 
- Cohort 1 (3 patients): 1 capsule (per os) at day1 and at day7, e.g., on a Tuesday and the Monday of the following week. Step up of dose regimen will then be as follows:
 
- Cohort 2 (6 patients): 1 capsule/day (corresponding to a maximum of 7 capsules) – 7 days (period of treatment)
 
- Cohort 3 (6 patients): 3 capsules/day (corresponding to a maximum of 21 capsules) – 7 days
 
- Cohort 4 (6patients): 3 capsules/day (corresponding to a maximum of 42 capsules) – 14 days
 
- 9 capsules/day (corresponding to a maximum of 63 capsules) – 7 days
 
 |
| ASSESSMENT/
SCHEDULE                   | 
Estimated inclusion period: 5 to 7 months
 
Calculated total duration of the study from start to last patient last visit: 7 to 9 months
                                                                                                                                                                                                                                                                                                                                                                                                                                                                                                                                                                                                                                                                         |

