### 8.2 STUDY DESIGN

#### 8.2.1 **Methodology and study phases**

Open-label, single-arm phase 1 study to evaluate the safety of MaaT033 in a step-up dosing design from 2 capsules 7 days apart to 9 capsules per day for 7 days.

Choice of cohort is based on the definition of maximum and minimum dose regimen acceptable for good compliance. 1 capsule per week is a reasonable minimum dosing while 9 capsules per day is a maximum we could define for such a population, already having quite important medications.

Our target dose is also in between these 2 cohorts, with 3 capsules per day. We decided to assess the impact of treatment duration with the comparison between a 7 days courses versus 14 days.

The study has the following phases:

- **Patient pre-screening phase** - Patients diagnosed with hematologic malignancy will be asked if they are willing to participate in this study by the investigating physician and will sign the informed consent form before any study examination. Only patients with neutropenia recovery will be finally included in the study.  
Neutropenia recovery is defined as a level of Absolute Neutrophil Count (ANC)  $\geq 0.5 \times 10^9$  cells/L.
- **Treatment phase** - The treatment will be started within 2 days after patient's inclusion. Clinical evaluation will be performed at baseline, at the interim visit (day7), before new cycle of chemotherapy start if any (day19 if not) and after new cycle chemotherapy if any (day44 if not). A step-up process will be applied between 5 different cohorts of patients and will depend on patient's tolerance of the treatment.
- **Follow-up phase:**  
Patient's overall status will be evaluated at D44 post inclusion (V4).  
AE/SAE collection will be performed from time of informed consent to V4.

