- **5th level of dose:** 6 patients will be treated with 9 capsules/day for 7 days. The Safety Committee (SC) will evaluate occurrence of Limiting Toxicity after the 6 patients will have completed V3. If two patients or more experiment a DLT, the study will be stopped and MTD will be considered as dose level 4. If one patient or less experiments a DLT, the MTD will be considered dose level 5.

**In any of the cohort 2 to 5, if any safety signal suggesting potential DLT is reported in 2 or more patient before the end of the inclusion of all patient of the cohort, inclusion of subsequent patient will be suspended and ad hoc meeting of the DSMB will be hold with all available information to assess those potential DLT and decide on the continuation or stopping the study.**

**A 24-hour gap should be respected between inclusions of the first 3 patients of each cohort to consider potential early or delayed toxicities.**

|                                                                                   |                    |                                                                      |
|-----------------------------------------------------------------------------------|--------------------|----------------------------------------------------------------------|
| [figure not shown] | DOCUMENT    | Protocol ID : MPOH05
EudraCT N° : 2019-004253-89
Version: 10.0 |
|                                                                                   | CIMON STUDY | Date : 04 MAY 2021
Page 25 / 70                                   |

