## 9 **STUDY POPULATION**

### 9.1 **INCLUSION CRITERIA**

Each patient must sign and date the consent form prior to initiating any study-related procedures.

To be eligible for study participation, a subject must meet all the following criteria:

- 1 Male or Female
- 2 Age  $\geq$  18 years
- 3 Patients diagnosed with AML defined according to WHO 2016 criteria with  $\geq$ 20% leukemic blasts in the bone marrow or high-risk myelodysplastic syndrome, receiving intensive chemotherapy
- 4 Patients healthy enough to likely receive their consolidation or second cycle of chemotherapy after induction chemotherapy
- 5 Patients healthy enough to likely receive HSCT
- 6 Informed written consent
- 7 Patient recovered from neutropenia

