### **11.1.3 Inclusion, Visit1 - D1 - TREATMENT START**

Screened patients with confirmed neutropenia recovery will be enrolled in the study after receiving oral and written information and giving informed consent.

The patient will be examined during a consultation by the physician to ensure that the patient fulfills inclusion and non-inclusion criteria.

Patient number will be composed of 9 digits: first 3 digits corresponding to country number, 3 digits corresponding to site number and last 3 digits corresponding to the first number available following that of previous patient included in the trial in the same site.

During this visit:

|                                                                                   |                    |                                                                      |
|-----------------------------------------------------------------------------------|--------------------|----------------------------------------------------------------------|
| [figure not shown] | DOCUMENT    | Protocol ID : MPOH05
EudraCT N° : 2019-004253-89
Version: 10.0 |
|                                                                                   | CIMON STUDY | Date : 04 MAY 2021
Page 36 / 70                                   |

- The physician will check inclusion and non-inclusion criteria to confirm patient is still eligible to the study since the screening period;
- Urine or serum pregnancy test will be performed;
- The physician will collect medical history, clinical evaluation (response to chemotherapy) and proceed to a physical exam including collection of vital signs;
- Blood samples (30mL) and fecal swab will be collected (See Table 1 for analysis details);
- The patient will be given a diary for compliance evaluation

If the seropositivity of EBV is already known and if a urine pregnancy test is performed instead of a blood test, screening period can be merged with visit V1, at the end of neutropenia.

**The MaaT033 treatment start the day of the inclusion visit, after collection of blood and feces samples for central laboratory.** Nasopharyngeal (or any other validated methods: salivary test, oro-pharyngeal test or other) SARS-CoV-2 results must be available before the first intake of MaaT033.

**The treatment should be started within 2 days after the documented end of neutropenia and it is highly recommended to take the first dose at the hospital**

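### The timing rules from neutrophil recovery to inclusion to first capsule disagree, and under one of them the 24-hour gap between inclusions does not guarantee a gap between first doses

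*Protocol*

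**What the plan says.** Inclusion criterion 7 in section 9.1 reads "Patient recovered from neutropenia" and carries no date or window. Section 8.2.1 supplies the threshold, an ANC of at least 0.5 x 10^9/L. The timing is spread over five places:

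- **Age of the ANC.** The note after the Table 1 footnotes: "Absolute neutrophil count will be assessed by the physician with local analyses performed within 3 days prior to V1".
- **Recovery to first capsule.** Section 11.1.3: "The treatment should be started within 2 days after the documented end of neutropenia". Table 1 note 1 says the same.
- **Inclusion to first capsule, same day.** Section 11.1.3: "The MaaT033 treatment start the day of the inclusion visit". The flow chart in section 4 likewise equates V1 with day 1 and the start of treatment.
- **Inclusion to first capsule, up to 2 days.** Section 8.2.1: "The treatment will be started within 2 days after patient's inclusion".
- **Stagger.** Section 8.2.2: "A 24-hour gap should be respected between inclusions of the first 3 patients of each cohort". The stated reason is to allow for early or delayed toxicity.

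**The concern.** Recovery from neutropenia is the entry condition for giving live microbiota to patients whom section 6.1.1 describes as immune-compromised. Because criterion 7 has no window of its own, sites must take one from the other passages, and these differ. The synopsis expects three to four sites, and each could reasonably apply a different window.

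The stagger has a related weakness. Toxicity follows dosing, but the 24 hours are counted between inclusions. If inclusion and first capsule fall on the same day, the distinction does not matter. If the capsule may come up to 2 days later, a site can respect the gap on paper while the first doses coincide or fall in reverse order.

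**Working it through.** No formula or figure in the plan has to be reproduced. The check enumerates the stated windows. It takes V1 as the inclusion visit and a count at or above the threshold as the document of recovery.

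**Inputs**
- ANC to V1: 0 to 3 days (note after the Table 1 footnotes).
- Inclusion to first capsule: 0 days (section 11.1.3, flow chart) or 0 to 2 days (section 8.2.1).
- Documented recovery to first capsule: at most 2 days (section 11.1.3, Table 1 note 1).
- Interval between consecutive inclusions: 24 h (section 8.2.2), taken at its minimum.

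**Formulas**
- Age of the ANC at first dose = (ANC to V1) + (inclusion to first capsule), limited to 2 days where the recovery rule is applied.
- First-dose gap = 24 h + lag of the later patient (B) - lag of the earlier patient (A).

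**Conflict between the ANC window and the recovery rule.** Recovery documented 3 days before V1, dosed at V1: 3 + 0 = 3 days. The ANC note is met and the 2-day rule is missed.

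**Results by the passages followed**

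| Passages followed | Maximum ANC age at first dose | First-dose gap |
|---|---|---|
| ANC note, same-day start, 2-day recovery rule (all rules kept) | 2 days | 24 h |
| ANC note, section 8.2.1, 2-day recovery rule | 2 days | -24 h to +72 h |
| ANC note, same-day start only | 3 + 0 = 3 days | 24 h |
| ANC note, section 8.2.1 only | 3 + 2 = 5 days | -24 h to +72 h |

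The range of the gap comes from 24 + 0 - 48 = -24 h and 24 + 48 - 0 = +72 h. For example, patient A is included on Monday and dosed on Wednesday, while patient B is included and dosed on Tuesday. For the first and third patients, included 48 h apart, the minimum is 48 + 0 - 48 = 0 h.

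The second row shows that keeping the 2-day recovery rule does not repair the stagger. If the ANC is taken on the day of inclusion, a lag of 2 days is still within that rule.

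**The case against.** The strongest reply is that these are upper limits of different lengths, not mutually exclusive rules. A patient whose recovery is documented 0 to 2 days before V1 and who is dosed at V1 satisfies every passage. That is correct, and a claim that the rules cannot all hold would be wrong.

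A reader might infer that the protocol permits a count 5 days old at first dose. Taken as a whole, it does not. That figure adds the ANC window to the section 8.2.1 lag and sets aside the 2-day recovery rule, the same-day start in section 11.1.3 and the flow chart.

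A reader might also infer that the 24-hour gap fails generally. It fails only for a site that uses the lag in section 8.2.1. Under the same-day start, 24 hours between inclusions is 24 hours between first doses.

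Nor is it fair to say that eligibility goes unchecked. Section 11.1.3 requires confirmed recovery and a recheck of the criteria at V1, and haematology is scheduled then. What remains is narrower: no passage requires the V1 neutrophil result to be read before the first capsule, whereas section 11.1.3 does require the SARS-CoV-2 result by then. The day-2 call, the ad hoc safety meeting and the cohort reviews are further protection, but they do not replace the stagger.

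It can also be argued that the documented end of neutropenia means the physician's confirmation at V1, which would remove the conflict with the 3-day window. The term is not defined. On that reading the 2-day rule no longer limits the age of the count, so the ambiguity still has to be settled.

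Finally, section 11.1.7 heads V4 as post-inclusion but times it from treatment start. That is a difference of at most 2 days within a +/-10-day window and does not matter.

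**Conclusion.** The inconsistency is real and stands in the current text. There are two separate conflicts: same-day start against a start within 2 days of inclusion, and a 3-day ANC window against a 2-day limit from documented recovery. Depending on the passages followed, the maximum age of the qualifying count at first dose is 2 or 3 days, or 5 days as a worst case across conflicting passages.

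The effect on the stagger is conditional. Under section 8.2.1 the first-dose gap can run from -24 h to +72 h. Under section 11.1.3 it stays at 24 h. The conflict over the start day therefore decides whether a stated safety measure does its job.

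These results assume that a qualifying ANC documents recovery, that inclusions are exactly 24 h apart, and that each lag can take any value from 0 to 48 h. How often sites would use the lag cannot be judged from the protocol.

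**What to change.** The sponsor should reconcile section 8.2.1, the flow chart in section 4, Table 1 note 1, the ANC note after the Table 1 footnotes and section 11.1.3. The time from inclusion to first intake, and the time from recovery or qualifying ANC to first intake, should then each be stated once and agree everywhere. In doing so it should define what counts as the documented end of neutropenia.

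Section 8.2.2 should then be reconciled with the result, so that the event from which the 24-hour gap is counted serves the toxicity purpose given there. Which event is the anchor and how long the intervals are is for the sponsor to decide.

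The cost is a wording amendment, and possibly an occasional short delay or a repeat of a routine blood count.

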## **11.1 VISIT SCHEDULE – CONDUCT OF THE STUDY**

### **11.1.1 Screening Phase**

Patients diagnosed with a hematologic malignancy will be asked if they are willing to participate in this study by the investigating physician and will sign the informed consent form as soon as possible after starting the induction chemotherapy and before any study examination. Only patients with neutropenia recovery ( $ANC \geq 0.5 \times 10^9$  cells/L) will be included in the study.

This screening period can be performed prior to V1 and can be scheduled at any time from the admission of induction chemotherapy. In this case:

- The physician will collect informed consent form before any study procedures
- The physician will collect demographic information and medical history
- The physician will collect a blood sample for EBV serology if the positivity of this parameter is not already present in patient's medical file.
- The physician will check and document birth control methods (appendix2).
- The physician will check inclusion and non-inclusion criteria;

This screening period can be merged with V1, at the end of aplasia, if the seropositivity of EBV is already known and if a urine pregnancy test is performed instead of a blood test.

Nasopharyngeal SARS-CoV-2 diagnostic test (or any other validated methods: salivary test, oro-pharyngeal test or other) must be performed within 3 days prior to treatment start.

### **11.1.2 Assessments performed during the entire study**

- The safety and tolerability of MaaT033 will be evaluated during the study with the collection of all AEs and SAEs (frequency, grade, relationship) from V1 to V4.
- Vital signs will be monitored at each visit. Vital signs, blood pressure (SBP and DBP) and heart rate in both supine position (after at least 10 minutes rest) and standing position (after 2 minutes), using an automatic sphygmomanometer.
- The compliance of MaaT033 will be evaluated by the patient with a diary to be completed from V1 to V3.
- Results from copro-cultures/hemo-cultures performed during patient's care will be collected in the electronic Case Report Form (eCRF).

### **11.1.3 Inclusion, Visit1 - D1 - TREATMENT START**

Screened patients with confirmed neutropenia recovery will be enrolled in the study after receiving oral and written information and giving informed consent.

The patient will be examined during a consultation by the physician to ensure that the patient fulfills inclusion and non-inclusion criteria.

Patient number will be composed of 9 digits: first 3 digits corresponding to country number, 3 digits corresponding to site number and last 3 digits corresponding to the first number available following that of previous patient included in the trial in the same site.

During this visit:

|                                                                                   |                    |                                                                      |
|-----------------------------------------------------------------------------------|--------------------|----------------------------------------------------------------------|
| [figure not shown] | DOCUMENT    | Protocol ID : MPOH05
EudraCT N° : 2019-004253-89
Version: 10.0 |
|                                                                                   | CIMON STUDY | Date : 04 MAY 2021
Page 36 / 70                                   |

- The physician will check inclusion and non-inclusion criteria to confirm patient is still eligible to the study since the screening period;
- Urine or serum pregnancy test will be performed;
- The physician will collect medical history, clinical evaluation (response to chemotherapy) and proceed to a physical exam including collection of vital signs;
- Blood samples (30mL) and fecal swab will be collected (See Table 1 for analysis details);
- The patient will be given a diary for compliance evaluation

If the seropositivity of EBV is already known and if a urine pregnancy test is performed instead of a blood test, screening period can be merged with visit V1, at the end of neutropenia.

**The MaaT033 treatment start the day of the inclusion visit, after collection of blood and feces samples for central laboratory.** Nasopharyngeal (or any other validated methods: salivary test, oro-pharyngeal test or other) SARS-CoV-2 results must be available before the first intake of MaaT033.

**The treatment should be started within 2 days after the documented end of neutropenia and it is highly recommended to take the first dose at the hospital**

The patient will receive the adequate quantity of capsules according to the cohort. Capsule containers will be presented in an adequate packaging. Detailed instructions related to IMP administration, documents to use and contact information in case of any issues are provided in the IMP Manual.

The treatment will not be started in case of presence of a toxic megacolon or gastrointestinal perforation, which constitute non-inclusion criteria.

All AE and SAE must be reported in the eCRF.

#### 11.1.4 Phone call - D2 (+2days)

A brief short call will be organized by the medical team after the first treatment intake (D2-D4). The aim of this call is to check patient's compliance (and completion of patient diary), to check any safety events observed by the patient and to remind patient to do the stool collection at D4 (+/- 2 days).

This phone call and any events discussed with the patient must be documented in source documentation.

#### 11.1.5 INTERIM PHASE, Visit 2 - D7 (D5-D9)

This visit will be performed 7 days (+/-2days) after the MaaT033 treatment start.

During this visit:

- The physician will proceed to a physical exam including collection of vital signs and clinical evaluation
- Blood samples (30mL) and fecal swabs will be collected (See Table 1 for analysis details)
- Evaluation of treatment tolerability, acceptability, compliance and safety
- Nasopharyngeal (or any other validated methods: salivary test, oro-pharyngeal test or other) and fecal SARS-CoV-2 tests will be performed

During this visit, the patient will report to the physician any adverse reaction or severe event occurred since the previous visit.

Regarding cohort4, the treatment will not be continued in case of presence of a toxic megacolon or gastrointestinal perforation, which constitute exclusion criteria.

All AE and SAE must be reported in the eCRF.

|                                                                                   |                    |                                                                      |
|-----------------------------------------------------------------------------------|--------------------|----------------------------------------------------------------------|
| [figure not shown] | DOCUMENT    | Protocol ID : MPOH05
EudraCT N° : 2019-004253-89
Version: 10.0 |
|                                                                                   | CIMON STUDY | Date : 04 MAY 2021
Page 37 / 70                                   |

